## Discussion

Despite the current global goal to eliminate pediatric HIV, to date few countries have assessed the population level impact of their PMTCT programs. We planned an ambitious study to measure the real-world effectiveness of Zimbabwe’s National PMTCT programme using innovative methodology to estimate the impact of PMTCT programs Option A and B+. Our design addresses key disadvantages of facility based evaluations of PMTCT programs by allowing us to assess HIV-free infant survival and MTCT at 9–18 months, thus taking into account HIV transmissions occurring during pregnancy, labor and breastfeeding among both women who access PMTCT services and those that do not [17].

Methodological issues in existing PMTCT effectiveness estimates limit our ability to assess progress towards global and country-level PMTCT elimination goals. WHO impact assessment guidelines suggest measurement of PMTCT program impact using mathematical/dynamic modeling, analysis of program data, serial cross-sectional serosurveys at 6–8 week immunization visits, cohort studies of mother-infant pairs attending health facilities, or serial cross-sectional serosurveys among community samples of infants [24]. In addition, WHO recommendations identify the MTCT rate and the HIV-free infant survival as key outcomes to measure effectiveness, with the latter being the gold-standard [25], as it accounts for infant infections *and* deaths. Outcomes should be measured post-breastfeeding, ideally at 18 months [15], as 15–20% of MTCT occurs during breastfeeding [3]. Despite these recommendations, most PMTCT effectiveness studies have used routinely collected facility-level program data and thus have not assessed population level impact [26]. Facility-based studies use existing health system mechanisms to identify infants, reducing the burden of capturing a study sample, which likely explains their predominance in evaluations. While these studies provide valuable information about the programs’ outcomes among their users, they do not measure population-level effectiveness. If coverage of such services (e.g., antenatal care, delivery, postnatal care) increases across developing countries, existing data sources may become suitable for PMTCT impact assessments. Meanwhile, however, if women not accessing services are more likely to be HIV-infected than women using health services, even if service uptake is ≥80%, facility-based studies could still overestimate program impact on MTCT.

Existing studies measuring MTCT do not capture infant deaths and hence likely overestimate impact (e.g., given high mortality among HIV-exposed and HIV-infected infants) [3, 27] and/or mask the intervention’s unintended effects (e.g., increase of infant deaths due to replacement feeding) [28, 29]. Studies utilizing prospective cohorts of mother-infant pairs allow assessment of MTCT and HIV-free infant survival, but is sensitive to LTFU, which reduces validity, and cohort effects where study participants may have better outcomes due to the care and follow-up they receive, or as a result of being observed (i.e., Hawthorne effect) [14]. Furthermore, the high cost of prospective follow-up remains a financial barrier for many impact evaluations.

We address these methodological gaps by conducting an impact evaluation of Option B+ using a community-based design that does not rely on facility level data, thus capturing PMTCT only among women who receive care at health facilities. While our serial community-based cross-sectional design has been used to assess Nevirapine-based PMTCT programs in four African countries [30], Option A in Zimbabwe [31], and Option B in Rwanda [32] and Zambia [28] it has not been used to assess the effectiveness of Option B+.

In addition to the lack of evidence on community effectiveness, no studies have assessed whether there is heterogeneity, based on type pf service delivery, in the potential impact of Option B+. The population-level effectiveness of PMTCT programs implementing Option B+ is likely to vary between health facilities [15] For example, providing lifelong ART to all women with HIV who enter the PMTCT cascade of services, as required by Option B+, requires decentralization of ART services as well as integration of PMTCT and ART services. The level of integration of these services may affect the program’s impact, as linkage to and retention in treatment and care is likely to be lower in facilities that refer women to ART centers compared to facilities are able to initiate women on ART. We know of no previous studies that have been able to determine impact heterogeneity of Option B+; specifically, we will conduct a novel analysis combining health facility data with aggregate population-level MTCT data from facility catchment areas. This analysis will also inform policymakers about which facility characteristics are associated with higher rates of HIV-free infant survival and less MTCT at 9–18 months.

Finally, the population-level benefits of Option B+ are predicated on mothers being retained in care for life, and our design will be one of the first population-based assessment of retention in HIV care up to 3 years postpartum among mothers who received Option B+. By simplifying service delivery and reducing the number of steps that mothers need to negotiate, Option B+ is expected to improve retention in care and adherence to ART. Given that the postulated benefits of Option B+ are predicated on HIV-infected mothers staying on ART beyond breastfeeding, our study design will test this assumption.

Our study is subject to limitations. Although our estimates account for transmissions occurring during the first 9–18 months of breastfeeding, HIV-exposed infants may still be breastfeeding at the time of the survey (median duration of breastfeeding is 17.8 months in Zimbabwe) [33]. Estimates of HIV-free survival for 9–18 month old infants may therefore overestimate HIV-free survival at 24 months (at the end of breastfeeding) and may result in an underestimation of MTCT. Nonetheless, estimates restricted to all HIV-exposed infants no longer breastfeeding at the time of our 2012 survey were comparable: 91.9% (95% CI: 86.8–95.1) HIV-free infant survival and 8.1% (95% CI: 4.9–13.2) MTCT [9].

If there is inadequate coverage of the full census, or inconsistency in the ability of health workers and survey staff to survey eligible mother infant pairs, the sample in our endline survey might represent a biased population. Recruitment in the community could vary during the periods of the year when there is greater temporary migration related to holidays or agricultural activities (going to the rural home for planting or harvest). In addition, although sampling procedures were modified in 2017–2018 to increase the rigor of our methodology, these changes may impact the comparability of our findings to previous survey rounds. Despite this, the added value of a more comprehensive strategy for identifying our target population of mother-infant pairs, combined with the utility of our modified approach in supporting MOH efforts to quantify Zimbabwe’s progress toward elimination, warrant this change. Finally, data will only be collected in five of ten provinces, although these were widely dispersed across the country and included major cities. Nevertheless, our findings from the 2012 survey were consistent with national-level data from the 2010–2011 ZHDS that similarly estimated that 12% of pregnant women were HIV-infected [33]. Despite these limitations, our unique design utilizing cross-sectional serosurveys at three time points will be one of the first impact evaluations of Option B+ using a community-based design. Our results will have direct relevance for Zimbabwe and other developing countries, as they will provide essential data to better understand the population-level impact and cost effectiveness of Option B+ and assess progress towards global MTCT elimination goals.

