## Methods/design

### Specific objectives

The specific objectives of this study include:Objective 1a, 1b: Compare the population-level impact of Option B+ on HIV-free survival and MTCT among infants 9–18 months of age in Zimbabwe to: a) standard of care before Option A; and b) Option A.Objective 2: Use facility and community level data to assess heterogeneity of the impact of Option B+ on HIV-free survival and MTCT among infants 9–18 months of age by the extent of integration of PMTCT and ART services at health facilities, among other factors.Objective 3: Assess retention of mothers in ART services 19–36 months postpartum.Objective 4a, 4b: Determine the cost-effectiveness of Option B+ compared to: a) the standard of care before Option A; and b) Option A.

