Secondary outcomes:3)Viral suppression: The proportion of HIV-infected mothers who are virally suppressed 9–18 months postpartum. The denominator (number of HIV-infected mothers) will be assessed as outlined above. The numerator will be assessed based on laboratory viral load test results. Mothers with viral load test results indicating < 1000 copies/ml will be classified as virally suppressed.4)Postpartum engagement in care (among mothers 19–36 months postpartum): The proportion of HIV-infected mothers who were initiated on ART and who continued ART. The denominator (number of HIV-infected mothers who were initiated on ART) will be assessed using: i) laboratory-confirmed HIV test results, or ii) information recorded on maternal health cards, when available, and iii) self-reported ART status. The numerator (number of HIV-infected mothers who were initiated on ART and continued ART after 19–36 months postpartum) will be assessed based on self-reported ART status at the time of the survey. Additionally, we will calculate the average time between delivery and discontinuation of ART among those mothers who did not continue ART.5)Heterogeneity of the impact of Option B+ on HIV-free survival and MTCT by the extent of integration of PMTCT and ART services at health facilities: Impact heterogeneity of Option B+ will be assessed using community-level cross-sectional serosurvey data as well as data on health facility characteristics from the 157 catchment areas selected as PSUs. The extent of integration of PMTCT and ART services at the facility level will be measured using multiple dichotomous variables such as: whether the facility offers both antenatal and labor/delivery services, whether the facility can initiate pregnant women on ART, whether the facility can continue women on ART after a certain number of months after delivery, whether the facility can offer ART services to male partners, and whether the facility can offer ART services to infants and children. Principal component analysis will be employed to estimate the factor loadings of these variables, in order to calculate an overall integration score per facility.6)Incremental cost effectiveness of Option B+: Assessed using effectiveness data (from the community-level cross-sectional serosurveys) along with costing data (from the 157 health facilities surveys). We will estimate the incremental cost-effectiveness ratio (ICER) of option B+ with respect to option A, and the ICER of option B+ with respect to pre-option A guidelines, as the ratio of the difference in costs over the difference in annually-adjusted effectiveness (for each of the two main outcomes: HIV-free infant survival and MTCT).

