For mothers at 19–36 months post partum, under the assumption of a 11.5% HIV prevalence among mothers in 2017–18, and taking into account variation in prevalence and refusal rates similar to those observed in the 2012 and 2014 surveys, we estimated that, in order to measure the proportion of mothers who continued ART after weaning, we would require a sample of approximately 1800 mother-infant pairs, of which approximately 200 mothers are expected to be HIV-infected.

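### The 19–36 month retention outcome is defined two ways (all ART initiators, or ART continued after weaning), and the window includes mothers who are still breastfeeding

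*Protocol article*

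**What the plan says.** All references are to the Protocol article.

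- **Specific objectives**, Objective 3: "Assess retention of mothers in ART services 19–36 months postpartum". Neither breastfeeding nor a test is mentioned.
- **Study measures**, secondary outcome 4: "The proportion of HIV-infected mothers who were initiated on ART and who continued ART", among mothers 19–36 months postpartum. The numerator "will be assessed based on self-reported ART status at the time of the survey". There is no condition on weaning. A time measure is added: "we will calculate the average time between delivery and discontinuation of ART among those mothers who did not continue ART".
- **Analyses**, Objective 3: the work is called mainly descriptive because the sample is small. It will look at the proportion who continued ART after weaning, split by ART use before PMTCT, and at the mean time from weaning to discontinuation among mothers who stopped.
- **Statistical power**: about 1,800 pairs, with about 200 HIV-infected mothers, are needed "in order to measure the proportion of mothers who continued ART after weaning".
- **Sampling strategy**: the 10% sample of mothers at 19–36 months is justified as showing engagement in care once breastfeeding is over.
- **Background**: the endline survey comes late enough for some mothers, not all, to have weaned.
- **Discussion**: "median duration of breastfeeding is 17.8 months in Zimbabwe", with the end of breastfeeding placed at 24 months. The Discussion also says that the benefits of Option B+ rest on women "staying on ART beyond breastfeeding, our study design will test this assumption".

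**The concern.** One objective carries two quantities. Under Study measures, a mother who is still breastfeeding and on ART at 20 months counts as retained. Under Analyses and Statistical power she does not belong in the denominator, because she has not weaned. The time origin differs too: delivery in one section, weaning in the other.

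The two quantities would coincide if every mother in the window had weaned, as Sampling strategy implies. The article's own figures say otherwise: the window opens 1.2 months after the median duration (19 − 17.8) and 5 months before the stated end (24 − 19).

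At stake is a figure that may be reported as post-weaning retention although some of the mothers in it have not weaned. If women are more likely to be on ART while breastfeeding, the error favours the programme. The Discussion's claim to test the assumption then adds weight that a descriptive proportion cannot carry.

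**Working it through.** **1. The plan's own figure.** Inputs: 1,800 pairs and 11.5% prevalence (Statistical power, 19–36 month sample); 2% refusal (Statistical power, main sample).

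1,800 × 0.115 × 0.98 = 202.9, which agrees with the stated approximate 200. No alpha, power or target precision is given for this objective, so there is no power statement to check.

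**2. Share still breastfeeding in the 19–36 month sample.** Document input: median duration 17.8 months. Assumptions: child ages uniform from 19 to just under 37 months (18 months wide), and a spread of durations, which the article does not give. Formula: the average over the window of P(duration > age).

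| Assumed distribution, median 17.8 | Still breastfeeding |
|---|---|
| Normal, SD 3 / 4 / 5 / 6 months | 3.8% / 5.9% / 8.1% / 10.2% |
| Lognormal, sigma 0.2 / 0.3 / 0.4 | 6.1% / 11.3% / 16.4% |
| Every mother breastfeeds to exactly 24 months | 5/18 = 27.8% |

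The last row is deliberately extreme, because it contradicts the median. If at most half are still breastfeeding when the window opens and all stop by 24 months, the ceiling is 0.5 × 5/18 = 13.9%. The lognormal with sigma 0.4 exceeds this only because its tail runs past 24 months.

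**3. Effect on the pooled proportion.** With a share f still breastfeeding, pooled = f × p_before + (1 − f) × p_after, so the excess over post-weaning retention is f × (p_before − p_after). The retention rates are assumed; the article gives none.

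| Assumed retention before / after weaning | f = 5% | f = 15% | f = 28% |
|---|---|---|---|
| 95% / 80% | +0.75 points | +2.25 | +4.2 |
| 90% / 70% | +1.0 | +3.0 | +5.6 |
| 95% / 60% | +1.75 | +5.25 | +9.8 |

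**4. Precision lost by restricting to weaned mothers.** Wald 95% half-width, 1.96 × √(p(1 − p)/n), at an assumed p = 80%:

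| Still breastfeeding | Weaned mothers, of 200 | Half-width |
|---|---|---|
| 0% | 200 | 5.5 points |
| 5% | 190 | 5.7 |
| 15% | 170 | 6.0 |
| 28% | 144 | 6.5 |

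These half-widths ignore clustering and treat all 200 HIV-infected mothers as ART initiators, so the real intervals will be wider throughout. They serve to compare one row with another.

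**5. What a test would need.** Analyses states no hypothesis and no threshold. Its one planned contrast is by ART use before PMTCT, not between breastfeeding and weaned mothers. The mean time from weaning to discontinuation is taken only among mothers who stopped, so it bears on timing but gives no rate of loss after weaning.

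**The case against.** The best defence is that the plan is more modest, and fuller, than one Discussion sentence suggests. Objective 3 only assesses retention, Analyses openly calls the work descriptive, and the time from weaning to discontinuation is planned alongside the proportion. Read plainly, ART continued after weaning concerns weaned mothers. Infant feeding and ART are asked about in both age samples (Endline survey of mothers/caregivers and their babies), so weaned mothers can be identified. How that denominator is built is the kind of detail an article leaves to the full plan.

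Much of this stands. The gap is one of definition, not of data. What does not fall away is that the sections shown define different populations and different time origins. That is a conflict in the text, not an omitted detail.

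A reader might infer three stronger things, none of which the article supports:

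- *That Objective 3 claims a test and fails to deliver it.* The claim is in the Discussion only. The assumption it names, that women stay on ART beyond breastfeeding, is a level among those who started ART. Estimating that level among weaned mothers needs no during-breastfeeding value. Such a value is needed only to separate loss before weaning from loss after it.
- *That the sample is heavily contaminated.* Under the normal spreads above, 34–42% are still breastfeeding at exactly 19 months, but that is only the youngest edge of the window.
- *That the conclusion should rest on a contrast with the 9–18 month sample.* That sample would hold about 13,000 × 0.115 × 0.98 = 1,465 HIV-infected mothers, but not all of them are ART initiators. The detailed items on engagement in care and ART interruption are described only for mothers at 19–36 months. Mothers weaned by 9–18 months are early weaners and may differ from later ones.

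**Conclusion.** The point holds as an inconsistency of definition with a modest numerical effect. Outcome 4 as defined in Study measures is retention among all ART initiators at 19–36 months. It is not the post-weaning proportion named in Analyses and Statistical power, and the window is not wholly after breastfeeding, as Sampling strategy treats it.

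About 4–16% of the sample would still be breastfeeding under the assumed spreads, and 28% in the extreme case. With assumed retention of 95% before and 80% after weaning, the pooled figure is about 1 to 4 points too high, against a half-width of 5.5 points. A clearly larger error needs both a wide gap in retention and a share near the extreme. The upward direction itself assumes that retention is lower after weaning.

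The Discussion's claim to test the assumption should read as a claim to describe it. This is a correction to one descriptive secondary outcome. The primary comparisons are not affected.

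**What to change.** 1. Reconcile Study measures with Sampling strategy, Analyses and Statistical power. Report ART continued after weaning among mothers who have weaned at interview, by time since weaning where numbers allow, and show still-breastfeeding mothers separately. If the overall 19–36 month proportion is kept, label it by months postpartum only.
2. State one time origin for time to discontinuation, delivery or weaning, and use it in both sections. If weaning is chosen, say how mothers who stopped ART before weaning are handled.
3. In the Discussion, say that the design describes whether mothers stay on ART beyond breastfeeding.
4. Optional and exploratory: a weighted comparison of current ART use with the 9–18 month sample, if the ART items prove to match. The conclusion should not rest on it, because it is cross-sectional and its weaned group consists of early weaners.

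Items 1 to 3 need no new data, since infant feeding is already recorded. The cost is a slightly smaller denominator and the small widening of the interval shown in step 4 of the working.
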